### Safety considerations

The training intervention is non-invasive, and no serious adverse events are anticipated. However, participants may experience frustration or mental fatigue. To ensure participant well-being, they will be closely monitored throughout the study, and any adverse events will be documented and promptly addressed. Participants will continue to receive their standard stroke rehabilitation care alongside their involvement in this study. In the unlikely event of a significant decline in a participant’s condition or upon their request to withdraw, they will be immediately withdrawn from the study, and data collection will cease. If a participant becomes ill or injured as a direct result of participating in this study, necessary medical treatment will be available to the participant at no additional cost.

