Participants will be initially screened for inclusion and exclusion criteria before undergoing a baseline assessment (see criteria below). Participants currently experiencing symptoms of spatial neglect, as determined by the baseline assessment, will be randomized, stratified by neglect severity, to one of two groups: experimental condition (PTM with 15-degree rightward-deviating goggles) or active control condition (PTM with 5-degree rightward-deviating goggles). Each participant will be assigned an “Assessor”, responsible for all assessments, and a “Trainer”, responsible for overseeing the PTM protocol training and scheduling. Trainers will observe participants during the first PTM session to ensure proper adherence to the protocol. Participants will then complete 10 daily training sessions over two weeks (5 days per week), with each session lasting approximately 15 minutes. Assessments will be conducted at 3 time points: baseline (T0), within one week after the final treatment session (T1; immediate follow-up), and within 4–6 weeks after the final treatment session (T2; one-month follow-up). After each PTM training session, after-effects will be measured, and the treatment and after-effects data will be stored on the iPad for later download. At T1, participants will independently set up and complete training in front of their Assessor to confirm their ability to follow the protocol as trained. The study will be conducted both in the community and across various hospital sites in Nova Scotia, Canada. Data collection is currently ongoing. This trial is open to recruitment from June 20^th^, 2024, to August 31^st^, 2027. Data collection is anticipated to be complete by September 2027, and results are anticipated by August 2028. See Fig 1 and Fig 2 for the study schedule and timeline, respectively.

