### Data collection and management

All research staff, including Assessors and Trainers, will receive standard training on data collection methods from the same supervisor. Study personnel consist of graduate-level clinical psychology students and supervised undergraduate students. All students must demonstrate competence in all tasks required for the “Trainer” and “Assessor” roles (e.g., administration of assessments) prior to data collection. Study personnel follow manualized protocols throughout the study.

Consent forms, participant demographics and health history, training logs, and data summaries will be securely stored using the Research Electronic Data Capture (REDCap) system hosted by Nova Scotia Health. Each participant will be assigned a unique identification number to ensure data de-identification. Other electronic data files will be stored on password protected computers or saved on a secure lab network behind a firewall. Access to electronic data is restricted to authorized personnel. Paper files will be stored in a locked laboratory with access limited to authorized personnel. If a participant withdraws from the present study or their participation ends early, all data collected up to the date they withdraw their consent and/or their study participation ends, will be maintained in the study records to be included in the study related analyses.

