To examine the impact of after-effects, a single average score over the two weeks of prism adaptation will be calculated. Then, we will examine the relationship between these mean after-effects scores and condition using an unequal-variances t-test. We will also explore the Pearson correlation between mean after-effects scores and the primary outcome.

An intention to treat analysis will be completed. We will also examine outcomes of participants who complete at least 80% of training and assessment components. Given the nature of our follow-up procedures, we expect low dropout. If missing data < 5%, listwise deletion will be used (complete cases) as when there is minimal missing data, more advanced strategies generally perform equivalently to listwise deletion [68]. If there is substantial missing data, it will be handled using multiple imputation using the Jomo [69] and mitml [70] packages in R software. In such a case, we will evaluate whether missing data is associated with any measured variables to incorporate into the missing data model.

All protocol deviations will be documented and reported to the principal investigator. Deviations that could affect participant safety will be promptly communicated to the ethics board. All deviations will be reviewed to assess impact, and corrective and preventative actions will be implemented as necessary to minimize recurrence.

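### A significant clinical decline ends all outcome collection even when consent stands, although the plan promises an intention-to-treat analysis

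*Protocol article*

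**What the plan says.** **Stopping rule (Safety considerations).** There are two triggers, a significant decline in the participant's condition (described as unlikely) and the participant's own request. Both have the same consequence: "they will be immediately withdrawn from the study, and data collection will cease". The section does not distinguish stopping Peg-the-Mole (PTM) training from stopping assessment.

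**Data kept (Data collection and management).** After withdrawal or early end of participation, "all data collected up to the date they withdraw their consent and/or their study participation ends, will be maintained in the study records" and used in the analyses. This covers data already in hand, not later visits.

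**Analysis (Statistical analyses).** "An intention to treat analysis will be completed". Participants who complete at least 80% of training and assessments are examined separately, so the intention-to-treat analysis is evidently meant to reach beyond them. On missing data: "Given the nature of our follow-up procedures, we expect low dropout". Complete cases are used if less than 5% is missing. Multiple imputation is used if missing data are substantial, after checking which measured variables are associated with missingness.

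**Dates (Study design and setting).** Recruitment runs to 31 August 2027, treatment takes two weeks, and T2 falls "within 4–6 weeks after the final treatment session". "Data collection is anticipated to be complete by September 2027".

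**The concern.** Ending assessment because a participant asks for it is ordinary. Ending it because the participant has become worse, while consent stands, is a choice made by the plan. It removes outcomes for a health-related reason, and someone whose condition has declined significantly may well score differently on Star Cancellation from otherwise similar participants who have not. The intention-to-treat comparison would then lack outcomes from people whom the plan itself told staff not to assess.

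No analysis plan can recover scores that the protocol says not to collect. Recruitment and data collection are under way, so each score lost in this way is lost for good. The trial is also small and already planned at a reduced power of 70%.

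**Working it through.** **1. What is lost, and when**

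| Timing of the decline | T1 score | T2 score |
|---|---|---|
| After randomisation, before T1 | not collected | not collected |
| After T1, before T2 | kept | not collected |

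T1 is the outcome of the first ANCOVA and T2 of the second, so either gap affects a main comparison.

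**2. What the missing-data rules do with it**

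The article gives no denominator for the 5% threshold. I read it as the share of participants with a missing outcome.

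- 5% of 42 is 0.05 × 42 = 2.1. Two losses are 2/42 = 4.8%, so complete cases are used. Three are 3/42 = 7.1%, above the threshold.
- Let p be the proportion of an arm lost and δ the covariate-adjusted difference between the mean of those observed and the mean that those lost would have had. The arm's complete-case mean is then off by p × δ. The treatment contrast is off by p₁₅δ₁₅ − p₅δ₅, which is zero only if the two products are equal.
- Multiple imputation removes this if, given the measured variables, the missing scores behave like the observed ones. The baseline score and any score retained before withdrawal help. Status after the decline is not assessed, because collection has ceased, so the condition may fail exactly where it matters.

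The article gives no expected rate of decline and no standard deviation for Star Cancellation, so no value can be put on p or δ.

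**3. Room for loss in the sample size**

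Inputs from the Sample size section: d = 0.61, R² = 0.40, alpha 0.05 (two-sided assumed), 21 per group at 70% power and 27 at 80%.

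Formula: noncentral t with ncp = d/√(1 − R²) × √(n/2) and df = 2n − 2 − k, where k is the number of covariates (1 to 3 tried).

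- n = 21: ncp = 0.61/√0.60 × √10.5 = 0.7875 × 3.240 = 2.55; power 70.1% (k = 1).
- n = 27: ncp = 0.7875 × √13.5 = 2.89; power 81.0% (k = 1).

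These inputs give exactly 21 and 27 as the smallest sufficient group sizes for k = 1, 2 and 3. The section also states d = 0.63, which would give 20 and 25. The stated sizes thus match d = 0.61 with nothing added for loss.

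| Participants analysed | Lost | Power (d = 0.61) |
|---|---|---|
| 42 | 0% | 70.1% |
| 40 | 4.8% | 67.9% |
| 38 | 9.5% | 65.6% |
| 36 | 14.3% | 63.1% |

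The loss rates are assumptions. To keep 21 per group with data would take 21/0.95 → 23, 21/0.90 → 24 or 21/0.85 → 25 per group at 5%, 10% or 15% loss.

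**4. Dates (minor)**

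For someone who starts training on 31 August 2027:

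- shortest path: 11 days of treatment + 28 days = 9 October 2027;
- longest path: 14 days + 42 days = 26 October 2027.

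Both fall after 30 September 2027, the latest reading of the anticipated completion. To reach T2 by then, training must start by 22 August (39 days) or, for the full window, by 5 August (56 days). With uniform accrual over the 1,167 recruitment days (assumption), this affects 42 × 9/1167 = 0.3 to 42 × 26/1167 = 0.9 participants. Any gap between enrolment and the first session adds to it.

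**The case against.** The other side has real points, and most limit the size of the problem.

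- **The trigger is narrow.** It is a significant decline, called unlikely, in a trial of a non-invasive intervention with no serious adverse events anticipated. This stands, and few participants may be affected.
- **Earlier data are kept.** Someone who declines after T1 still contributes to the T1 analysis. This stands.
- **Some loss is unavoidable.** A participant who is very unwell may be unable to do a paper-and-pencil cancellation test under any rule. This stands, and the fix allows for it.
- **Bias in the contrast needs the arms to differ.** They differ only in prism strength, and the article suggests no reason why decline would differ. This stands as a limit. Balance is plausible but not assured with 21 per arm.
- **There is a missing-data plan.** Complete cases below 5% is a stated choice with a cited justification, and the imputation model is to use variables associated with missingness. This reduces the problem, but it does not answer a loss that depends on the unseen score.

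Three stronger readings are tempting, and the documents do not support them. A reader might infer that the intention-to-treat analysis becomes an analysis only of those who did not deteriorate; the rarity of the trigger and the retained data speak against that. A reader might infer that imputation would treat decliners simply as stable participants; it would condition on their retained scores and on related variables. And a reader might infer that September 2027 is a cut-off that cancels late T2 visits. It is a forecast, nothing says such visits would be skipped, and results are not expected until August 2028.

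**Conclusion.** The point holds in a limited form. As written, the safety rule ends T1 and T2 assessment for a health-related reason while consent stands, and this works against the promised intention-to-treat analysis. Scores lost this way are plausibly informative, and neither planned missing-data method can be relied on to correct for that.

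The direction and size of any bias are unknown. The loss of precision can be stated: about 2 percentage points of power for two lost outcomes (70.1% to 67.9%) and about 4.5 for four (70.1% to 65.6%), assuming d = 0.61, R² = 0.40, a two-sided 5% test and complete-case analysis. The plan should be changed because the remedy is cheap and lost assessments cannot be recovered.

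The date mismatch is a scheduling inconsistency affecting fewer than one expected participant under uniform accrual, and none if the target is reached early enough.

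**What to change.** 1. Leave the safety rule for treatment as it is, but separate stopping PTM from stopping follow-up.
2. State that T1 and T2 assessments are still sought, where the participant is able, from everyone randomised unless consent to data collection is withdrawn.
3. Record the reason for stopping, and whether it is the training, the assessments or both that end. The analysis can then distinguish clinical decline from withdrawal of consent.
4. Reconcile the dates under Study design and setting: either move anticipated completion to late October 2027 or later, or close recruitment early enough for the last T2 window to end in September 2027.

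The cost is revised protocol wording with ethics-board review, and a few visits to participants who have stopped training. Those visits are already in the schedule for everyone else.

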### Knowledge translation and dissemination

Our team will actively engage in a range of knowledge translation activities to disseminate our findings. These will include presenting results through media outlets, conducting talks for stroke support groups, participating in relevant conferences, and clinical rounds at partnered hospitals. The study protocol will be available for public access. However, given the clinical nature of the dataset collected in the present study, only group-level data will be available upon request. Protocol modifications that have ethical considerations will be reported to the Nova Scotia Health Research Ethics Board and study participants. All protocol modifications will be reported during the final publication of study results.

## Discussion

Spatial neglect is a common disorder post-stroke linked to poor rehabilitation outcomes and reduced independence in ADLs. There is currently an unmet need for an accessible, effective, and feasible intervention for the treatment of this condition. The present ongoing study aims to address this gap by conducting a randomized, controlled, double-blind, clinical trial to evaluate the effectiveness of using PTM with 15-degree deviating prism goggles, compared to an active control condition. The study will assess both short-and longer-term treatment effects on neglect severity.

This clinical trial uses an innovative protocol that allows for treatment in both inpatient and home settings, which enhances accessibility for individuals with spatial neglect. The gamified aspects of PTM are designed to increase engagement and adherence, potentially improving participants’ recovery and quality of life. Results from this study will provide valuable insights into the feasibility and acceptability of implementing PTM in diverse settings, as well as identifying patient characteristics associated with a positive response to treatment. Ultimately, if the intervention is feasible and effective, it could contribute to improved continuing care, enhanced quality of life after stroke, and increased access to rehabilitative services for those with neglect.

There are several limitations of the present study design and implementation that are important to note. First, although conducting treatment and assessments in participants’ homes and inpatient units enhances accessibility and adherence, data collection within specific geographic regions may limit the generalizability to the broader population of stroke survivors given the heterogeneity of spatial neglect. Second, although all participants receive standardized training on PTM use, differences in familiarity, confidence with, and attitudes toward technology may influence treatment adherence, particularly among older adults [71]. Third, despite procedures implemented to ensure standardization (e.g., standardized set-up, manualized training, written instruction sheets), the home-based context introduces potential variability between sessions and participants due to environmental factors (e.g., distractions) and user error. Finally, the relatively short follow-up period limits the ability to draw conclusions about the durability and long-term maintenance of treatment effects. These limitations will inform refinements to future iterations of the protocol to optimize standardization and scalability.

From a clinical perspective, previous work has emphasized the broader therapeutic value of structured physical therapy and exercise in improving neuropsychological outcomes. Building on this, our study highlights how game-like, home-friendly approaches can enhance engagement and rehabilitation effectiveness in disorders such as spatial neglect [72]. If PTM proves to be an effective, feasible, and engaging treatment for spatial neglect, findings from the present study could help inform clinical practice by promoting scalable, accessible, home-based rehabilitation strategies. Additionally, the results may guide the development of evidence-based recommendations for spatial neglect care after stroke. Consistent with recent work on other at-home interventions (e.g., ecological PA, telerehabilitation, and virtual reality interventions) [73,74] the present study highlights the importance of accessible, technology-supported rehabilitation strategies to improve patient engagement in post-stroke rehabilitation and long-term functional outcomes.

Future research should examine the optimal dose of PTM, including session length, frequency, and total number of sessions needed to maximize therapeutic benefits [33]. Long-term maintenance of treatment effects should also be examined. Additional studies should also evaluate the scalability, cost-effectiveness, and integration of PTM within existing stroke rehabilitation pathways, including implementation across multiple clinical and home-based settings.
